### Study Design

This trial adopts a cluster randomized design of a deprescribing intervention delivered over 24 months in primary care patients. The clustering component is intended to minimize the potential for contamination and is conducted at the level of primary care provider. Figure 2 provides an overview of the general study design noting the level of randomization and schedule of outcome assessments. A unique feature of the design intended to address a key gap in the existing literature is the long duration of follow-up, allowing us to detect trends in changes in outcomes up to 24 months.

### Study Sites and Recruitment Procedures

Recruitment is conducted within primary care practices of health systems in central Indiana, including Indiana University Health and the Community Health Network. Indiana University Health is a large, quaternary care state-wide health system. Primary care locations in the greater Indianapolis area were prioritized based on the original plan for in-person recruitment. Community Health Network is a large tertiary care regional network located in central Indiana. Select primary care locations in the greater Indianapolis area were invited to participate based on potentially eligible population density and availability of support from clinical pharmacists.

Primary care leaders provide approval to conduct proposed studies in primary care environments and within patient panels. Searchable elements from electronic medical records are used to identify providers with potentially eligible patients, and group those lists of patients by providers. While we do not collect data directly from providers, the intervention may influence the care some of their patients receive (particularly those providers randomized to the intervention group), making it ethically appropriate to allow providers the opportunity to opt out. Thus, prior to recruitment of potentially eligible patients, providers receive information about the study objectives, procedures, and expectations and are offered an opportunity to not participate (thus excluding all patients under their care) or exclude some of their patients. See figure 3 for the timeline of recruitment, intervention, and assessment of the R2D2 trial. This opt out approach was recommended by primary care leadership at participating sites.

Recruitment of potentially eligible patients utilizes lists generated from searchable criteria from electronic medical records, including age, medication and visit history, diagnostic data, and participating provider. With telephone-based recruitment, the Informed Consent Form and HIPAA forms are provided to the participant by postal or electronic mail, or left at an agreed-upon location based on the participants comfort. The person obtaining consent arranges a time to discuss the study with the participant by telephone. During this telephone meeting, the person obtaining consent reviews the Informed Consent and HIPAA and answers any questions. After all questions have been addressed, the participant is asked to sign and date these study documents, then to return them by mail or email. The personnel obtaining consent signs and dates each returned document and proceeds with study procedures. This person is blinded to randomization status.

### Eligibility criteria:

Eligible individuals are community-dwelling older adults without a diagnosis of ADRD who receive primary care from two regional healthcare systems in Indiana. We intentionally exclude those with ADRD because prior work suggests this population is not likely to benefit from the intervention.^16
26
35^

#### Inclusion Criteria:

Age 65 years and olderAt least one office visit to their primary care physician within the previous 12 monthsUse of at least one strong anticholinergic medication in the previous 2 weeks OR a ratio of total standardized days exposed within the prior 365 days of at least 0.4 or higher.^7
11
14^Original criteria required the presence of subjective cognitive dysfunction by meeting either (a) or (b) of the following criteria:
A response of “somewhat worse” or “much worse” to the SCD screening question: “In general, how would you describe your memory as compared to 10 years ago? Response offerings are: much better / somewhat better / about the same / somewhat worse / much worse. This item is derived from the Sydney Memory and Aging study^36^ and is comparable to items used to document self-report of memory in the HRS-AHEAD Study (1993 to present), the IQCODE questionnaire for cognitive decline in the elderly,^37^ and items used in the Pittsburgh cohort studies of aging.^38^A score of 5 or less on the Six-Item Screener (SIS).^39^ The SIS is a global measure of cognitive status that assesses three-item recall and orientation to year, month, and day of the week.^39^ The SIS screening test was developed in the primary care population at Eskenazi Health and validated in a racially diverse population. Scoring is determined by the number correct with a range of 0–6, where higher scores indicate better cognition; a score of ≤ 5 has a sensitivity of 97.7% and specificity of 49.3% for identifying cognitive impairment in primary care older adults.^39
40
41^Able to communicate in EnglishAccess to a telephone.

After reviewing the initial 6 months of recruitment, the study team recognized that certain eligibility requirements significantly compromised the ability to meet recruitment targets. With approval from the Data and Safety Monitoring Board (DSMB), we subsequently expanded criterion 2 to include those who achieved a calculated measure of anticholinergic medication exposure based on medical record data from the prior 12 months, and removed the requirement for criterion 4a and 4b (presence of subjective cognitive decline defined through either approach). We continued to collect data on the presence of subjective cognitive complaints in a similar manner as outlined above.

#### Exclusion Criteria:

Permanent resident of an extended care facility (nursing home)Diagnosis of schizophrenia, bipolar disorder, or schizoaffective disorder defined by ICD9/10 codesDiagnosis of ADRD as determined by either:
ICD-9/ICD10 codes, orCurrent use of a medication for ADRD (donepezil, rivastigmine, galantamine, or memantine), orA pattern of responses to the Functional Activities Questionnaire (FAQ) that suggest a combination of assistance and dependence in daily activities that is consistent with level of function in ADRD (i.e., exclude if ≥ 3 FAQ items are scored at “requires assistance,” or if ≥ 1 FAQ item is scored at “dependent”).^42^

### Randomization procedures

In this cluster randomized trial, randomization occurs at the level of primary care provider in a 1:1 proportion between intervention and usual care using a randomization list with a computer-generated random scheme in random blocks of 4 or 6 stratified by healthcare system. Research staff are blinded to provider allocation status at the time of recruitment and throughout the study to avoid bias in data collection.

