### Analysis Plan

The cluster randomized trial design will be used by randomizing primary care physicians (PCP) into the intervention or usual care arms. Outcomes will be collected and analyzed at the patient level. We will examine assigned randomization against the computer-generated randomization scheme to ensure randomization validity. Patient characteristics between the two groups will be compared using mixed effects models for continuous variables and generalized estimating equations for categorical variables while adjusting for random PCP effects. We will examine the distributions of continuous variables and use alternative approaches such as transformation or nonparametric methods in cases of violation to the normal distribution assumption. We will also examine the frequency distribution of all categorical variables and adopt exact inference procedures in cases of zero or small cell size. Any baseline variable that is found to be significantly different between the two groups will be included as a covariate in the analyses outlined below.

An intension to treat approach will be used in the analysis of all outcome measures. Composite cognitive scores collected at 6, 12, 18 and 24 months will be used as the primary outcome variables in mixed effects models. An indicator variable for intervention group (intervention vs usual care), time, interaction between group and time, and baseline cognitive scores will be included as independent variables as well as significant factors from the baseline comparison. PCP will be used as random effects to adjust for within-physician correlations. Significant group and time interaction or significant group main effect will indicate differences in cognitive function between the two groups. If significant interactions between group and time are found, post-hoc analyses will be conducted to determine the times when the two groups have significantly different cognitive scores. A significant main group effect in the absence of a group-by-time interaction would indicate differences between groups in cognitive function at all follow-up time points.

In a second set of models, we will determine whether differences between groups were accounted for by decreases in total exposure to anticholinergics from baseline to 24 months. For each medication, standardized daily exposure will be calculated using standardized daily dose as in the study by Gray^7^ and validated in our prior work^14
17

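### Randomisation is stratified by healthcare system but the stated primary model omits it; if the systems differ in follow-up cognition, the group main effect loses some precision

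*Protocol article*

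**What the plan says.** Under Randomization procedures, providers are allocated "in a 1:1 proportion between intervention and usual care", "in random blocks of 4 or 6 stratified by healthcare system". Study Sites and Recruitment Procedures names the systems, "including Indiana University Health and the Community Health Network", and the eligibility criteria speak of two.

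The Analysis Plan sets out the primary mixed model for the composite cognitive score at 6, 12, 18 and 24 months. Besides the group indicator, "time, interaction between group and time, and baseline cognitive scores will be included as independent variables as well as significant factors from the baseline comparison". Clustering is handled by one further term: "PCP will be used as random effects to adjust for within-physician correlations". Healthcare system is not listed.

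The route for further covariates is also fixed: "Any baseline variable that is found to be significantly different between the two groups will be included as a covariate". For a categorical variable such as system, the baseline comparison uses "generalized estimating equations for categorical variables while adjusting for random PCP effects". The PROMIS and HUI models follow the same pattern, and the exposure model adjusts for significant baseline variables and PCP effects. The plan counts either a significant group-by-time interaction or a significant group main effect as a difference between arms.

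**The concern.** Stratified blocking makes the two arms contain nearly equal shares of each system's PCPs, so any stable difference between systems largely cancels from the arm comparison. A model without system does not know this. It reads the between-system difference as ordinary variation among PCPs and charges it to the standard error of the group effect. The PCP random effect absorbs that variance but does not recover the precision that the stratification provided.

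The covariate rule makes the omission close to permanent. It selects variables that differ between arms, and stratification exists to stop this variable from differing. So the article does not merely leave the matter open: it states a rule under which the one factor used in the randomisation will almost never enter the analysis.

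At stake is some power for the group main effect, in a trial planned at 80%.

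**Working it through.** **The plan's own figures.** Design effect 1 + (6 − 1) × 0.05 = 1.25; 96 × 1.25 = 120 completers per group; 120 / 0.70 = 171.4, rounded up to 172; 2 × 172 = 344. These steps reproduce. Nothing below depends on how the 96 was obtained.

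**Inputs from Sample Size and Rationale.** ICC 0.05; 6 patients per physician; within-subject correlations 0.3, 0.2 and 0.1 at 6, 12 and 18 months apart; 80% power; α = 0.05.

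**Assumptions, because the article gives no figure.**
- A share p of PCPs is in one system, with p = 0.5 as base case.
- The systems differ by d SD in follow-up cognition after baseline adjustment, the same at every visit; d runs from 0 to 0.3.
- The ICC of 0.05 applies within system, and the test is two-sided.
- No variance reduction from the baseline score is credited. Crediting it would raise the ratios below for a given residual d.

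**Step 1: will the covariate rule pick up system?** Block randomisation of about 40 PCPs (240 completers / 6) in two strata was simulated. A cluster-adjusted test of system by arm was significant in about 0.1% of trials (0 to 0.2%) with unequal patient panels and in 0% with equal panels. A test ignoring clustering would be significant in about 16–20% with unequal panels, but the plan specifies PCP-adjusted tests.

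**Step 2: variance of a PCP mean within system.**
- Averaging four visits multiplies the patient-level variance by [4 + 2(3 × 0.3 + 2 × 0.2 + 1 × 0.1)] / 16 = 6.8 / 16 = 0.425.
- v = 0.05 + 0.95 × 0.425 / 6 = 0.117.
- For a single visit, v = 0.05 + 0.95 / 6 = 0.208.

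**Step 3: inflation of the main-effect standard error.** Leaving system out adds p(1 − p)d² to the apparent variance of a PCP mean, so SE without the term / SE with it = √(1 + p(1 − p)d² / v).

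| d (SD) | 0.25 d² | SE ratio, four-visit mean | SE ratio, single visit |
|---|---|---|---|
| 0 | 0 | 1.00 | 1.00 |
| 0.1 | 0.0025 | 1.01 | 1.01 |
| 0.2 | 0.0100 | 1.04 | 1.02 |
| 0.3 | 0.0225 | 1.09 | 1.05 |

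With an 80:20 split, p(1 − p) = 0.16 and the four-visit ratios at 0.2 and 0.3 SD fall to √(1 + 0.0064 / 0.117) = 1.03 and √(1 + 0.0144 / 0.117) = 1.06.

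**Step 4: power.** A test with 80% power when adjusted has a standardised effect of 1.96 + 0.84 = 2.80. Dividing this by the ratio r gives power Φ(2.80 / r − 1.96), which is 80, 79, 77 and 73% for d = 0, 0.1, 0.2 and 0.3. This slightly overstates the loss, because the true spread of the estimate stays at the adjusted SE. Using Φ(2.80 − 1.96 r) instead gives 80, 79, 78 and 75%.

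**Step 5: false positives.** In simulation (four-visit mean, 50:50 split), the nominal 5% main-effect test without system rejected in 5.3, 5.1, 4.5 and 3.4% of null trials for d = 0, 0.1, 0.2 and 0.3. With the term the rate was 4.5–5.7%.

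**Step 6: group-by-time interaction.** With 40 PCPs of 6 patients and a time-constant d, the simulated SE of the slope contrast was 0.054 with or without the system term, at d = 0, 0.3 and 0.5. In the same runs at d = 0.3, the main-effect SE was 0.1183 without the term and 0.1074 with it, a ratio of 1.10 that agrees with Step 3.

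**The case against.** The strongest reply is that the harm is conditional. The model already contains the baseline cognitive score, so only a residual difference between systems matters, and the article reports none, raw or adjusted. With no residual difference nothing is lost, and up to 0.2 SD the inflation is at most about 4%. If the planned ICC of 0.05 is taken to include the system component, 0.2–0.3 SD would make system alone 20–45% of all between-PCP variance (0.010 / 0.05 and 0.0225 / 0.05), which nothing in the article supports. The PCP split is also unknown, and an unequal one shrinks the effect. All of this stands, and it is why the size is given as a range starting at zero.

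A reader might infer that the standard error is certainly too large, or that the analysis is invalid because it departs from the randomisation. The document supports neither. The first needs a system difference that it does not give. As to the second, the omission makes the test conservative, and no bias or excess of false positives is shown. Nor is all power affected: the group-by-time interaction, the other route to declaring a difference, is untouched unless the system difference changes over time.

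It can also be said that a condensed article may leave stratification covariates to the full analysis plan. That would answer silence. Here the article names the model terms and fixes a rule for adding others, and that rule works against this factor. It is a general rule and not aimed at system, but the result is the same.

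**Conclusion.** The point holds as a modest matter of precision. The stated model omits the stratification factor, and the stated covariate rule will almost never restore it. If the systems differ in follow-up cognition after baseline adjustment, the standard error of the group main effect is overstated: by about 1% at 0.1 SD, 4% at 0.2 SD and 9% at 0.3 SD. At 0.3 SD, 80% power falls to roughly 73–75%. If they do not differ, there is no loss. These figures rest on an assumed 50:50 split, the planning ICC and cluster size, the mean of four visits and a difference constant over time. The loss becomes material only from about 0.3 SD. Conclusions from a significant result would not be endangered.

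**What to change.** State in the analysis plan that healthcare system is a fixed effect in the primary cognitive model whatever the baseline comparison shows, and include it likewise in the PROMIS, HUI and anticholinergic exposure models. The baseline-significance rule should not govern this term.

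The cost is one model term and one degree of freedom. No new data are needed, because each provider was randomised within a system and so the system is known for every participant. Data collection is expected to run to July 2026, so on the article's timeline the change can be recorded before the analysis.

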### Deprescribing Intervention

The deprescribing intervention is executed through a trained clinical pharmacist employed within each study site, called a Deprescribing Care Coordinator (DCC). This model is developed from prior experiences in anticholinergic deprescribing in our local institutions.^33
43–45^ Training is provided in geriatric care (particularly high risk medications and appropriate alternatives), educational methods, titration and monitoring schedules, and behavioral economic principles that encourage communication and successful deprescribing attempts. The latter emphasizes the use of messengers, identifying incentives, and setting defaults that can support deprescribing. The trained clinical pharmacists communicate the deprescribing attempt with the patient, providers, and pharmacy as needed to coordinate the transition from a high-risk anticholinergic medication to a safer alternative.

The following general steps are conducted by the DCC to complete the deprescribing process: 1) Clarifying the indication for the anticholinergic through medical record review and participant interview, 2) Education of potential risks of cognitive impairment in older adults, 3) Making a shared decision to deprescribe among participant, caregiver (as needed), and providers, 4) Identifying an appropriate alternative (not an anticholinergic medication or potentially inappropriate medication for older adults as defined by the American Geriatrics Society’s Beers Criteria ^®^^46^) if desired, 5) Communicating the deprescribing plan with the appropriate provider(s), and 6) Monitoring and revising the plan as needed. The deprescribing process is initiated within seven days of enrollment, and most deprescribing is expected to be completed within four to six weeks after enrollment (see appendix

The participant, pharmacist and physician will decide which deprescribing approach is most appropriate. Timelines for taper schedules will follow recommendations in the appendix regardless of the intent to replace the anticholinergic with a non-anticholinergic alternative or non-pharmacologic approach. Modification to deprescribing tapering intervals will be allowed based on clinical judgment of the research or clinical staff (DCC or provider physician) along with monitoring of symptom burden. If multiple anticholinergics are being used concurrently, a drug-specific decision on the deprescribing approach will be necessary, and only one deprescribing attempt will be performed at a time. According to the deprescribing protocol, tapering/discontinuation attempts will follow either a concurrent crossover, delayed crossover, or tapered discontinuation plan (see Appendices 1 & 2 for additional recommendations); however, this process is subject to interruption and delay based on clinical context for each participant and agreement between the DCC and providers caring for the participant.

The design of the intervention acknowledges a number of factors that influence deprescribing success as recognized in the general model published by Linsky and colleagues (see figure 4 below).^47^ These include patient factors, provider considerations/factors, and the process of deprescribing (medication orders, monitoring plans and adjustment based on patient-reported outcomes). Furthermore, our model of deprescribing anticholinergics includes the influence of behavioral economics on each of these factors. Recognizing the role of the messenger, incentives, and default settings in the process of deprescribing is addressed in the deprescribing protocol and contributes to the implementation of the intervention.

### Usual Care

The group randomized to usual care will receive educational material via traditional mail that reviews risks of polypharmacy, but no information specific to anticholinergic medications. The material will direct participants to their prescribers or pharmacists if they have concerns about their medications. The information will be delivered approximately 7 days following enrollment to coincide with the onset of the intervention in those randomized to the intervention group.

### Measures

The primary outcome measure is cognitive performance in three critical domains relevant to the diagnosis of dementia that include information processing speed, memory, and executive function. In older adults, these domains have been shown to be impaired by anticholinergic medications.^48^ We originally selected four cognitive tests based on a systematic review of 78 RCT’s among healthy adults that identified tests that were sensitive to the adverse cognitive effects of medications.^48^ These included the Digit Symbol Substitution Test (information processing speed), Buschke selective reminding task (memory and new learning), Choice Reaction Time and Trail Making Test Parts A and B (executive cognitive function).^49–51^

Because approval to initiate recruitment was received only days before in-person research operations were interrupted by the COVID-19 pandemic, we identified an alternative battery of cognitive tests encompassing the same domains but with the ability to be administered remotely with equivalent validity. Therefore, we modified the battery for the primary outcome to include the Symbol Digit Modalities Test (information processing speed), Hopkins Verbal Learning Test (memory & new learning), Oral Trails Making Test (executive function), and Controlled Oral Word Association and Semantic Fluency tests (executive function including phonemic and semantic fluency). These tests have been used by our team with fidelity across telephonic modes of delivery.^52^

We will form an overall cognitive composite score as the average of each cognitive measure’s z-score, which is constructed by subtracting the mean baseline scores and dividing by the baseline standard deviation. Cognitive measures will be taken at baseline, 6, 12, 18, and 24 months during scheduled outcome assessment visits conducted by telephone. Parallel alternate forms will be used for all tests (3 versions each) presented in a counterbalanced fashion throughout the trial thus minimizing confounding due to learning effect.

The study intervention proposes to reduce exposure to medications that are prescribed to manage symptoms of depression, anxiety, insomnia, and pain. We will use the Patient Reported Outcomes Measurement Information System (PROMIS) to capture the four patient safety outcomes. PROMIS was developed by the National Institute of Health. It is unique in its ability to standardize scores across diagnoses and symptoms, it possesses excellent reliability and validity, and it is inclusive of diverse population characteristics and backgrounds.^53^ The PROMIS profile-29 (www.nihpromis.org) includes brief scales for several domains; we will use four-item scales for depression, anxiety, and sleep disturbance (insomnia), and a 3-item pain intensity scale.^53^ These and other safety measures (see below) will be collected at baseline and months 6, 12, 18, and 24. Comprehensive scoring manuals are available for each measure with guidance for interpreting individual and composite scales. Each PROMIS raw score can be converted to a T-score where 50 represents the general population norm for that symptom and each 10-point deviation represents one standard deviation (SD) from the population norm.

We will use the 15-item Health Utility Index (HUI) to determine each participant’s health-related quality of life (HRQOL) at baseline and months 6, 12, 18, and 24.^54^ The HUI is a utility-based HRQOL instrument applied in patients with a wide range of medical conditions. It has eight attributes: vision, hearing, speech, ambulation, dexterity, emotion, cognitive function and pain. The individual health domain scores range from 0.00 (maximum impairment) to 1.00 (no impairment) and the multi-attribute (HUI) scores, a multiplicative function of individual attribute levels, range from 0.36 to 1.00 with anchors 0.00 = dead and 1.00 = perfect health.

To assess adverse events, two methods are planned: 1) a single-item question will be asked at each follow-up assessment to collect self-reported adverse events, and 2) acute care utilization, defined as emergency room or hospitalization recognized through our statewide health information exchange (Indiana Network for Patient Care). Both methods will be reviewed and summarized at each meeting of the DSMB.

The presence of APOE 4 alleles may modify the effect of anticholinergics on cognitive impairment, therefore, we originally planned to collect blood from each participant at baseline to include as a covariate in the responder analysis (secondary aim). However, given the COVID-19 interruption of in-person research, we revised our procedures to collect the APOE 4 variable remotely through saliva samples. Genomic DNA will be extracted from saliva samples using the DNeasy Blood & Tissue Kit (Qiagen, Inc., Valencia, CA) according to the manufacturer’s protocol. Sample kits will be distributed by mail to participant homes with instructions on how to complete and with pre-paid packaging to return to the Indiana Biobank for storage and processing. The sample kit will be distributed at the beginning of the study, but may be completed at any time of participation, and must be completed before 24 months or withdrawal from the study. Extracted DNA will be sent to LGC Limited, the preferred genotyping resource of the Indiana Alzheimer’s Disease Center and the Indiana Clinical and Translational Sciences Institute.

Because individual differences have potential to modify treatment outcomes, we will measure the following demographic and clinical factors: age, self-reported race, self-reported gender, self-reported years of education, and relevant clinical diagnoses impacting cognition such as depression, cardiovascular disease, stroke, and diabetes as we have done in prior studies.^8
17
55^ These demographic variables will be collected at baseline while diagnoses from the electronic medical record will be collected at baseline and 24 months (see Table 1). We will collect medication use through both self-report at baseline and each outcome assessment, and extract prescribed medications (medication orders) from electronic medical records prior to enrollment as well as during the 24-month study period.

